## Abstract

**Background:**

Endogenous Cushing’s syndrome (CS) results in increased cardiovascular (CV) morbidity and mortality. So far, most studies focussed on distinct disease entities rather than the integrity of the CV system. We here describe the design of the Cardiovascular Status in Endogenous Cortisol Excess Study (CV-CORT-EX), a study aiming to comprehensively investigate the health status of patients with endogenous CS (with a particular focus on CV phenotypes, biochemical aspects, quality of life, and psychosocial status).

**Method:**

A prospective non-interventional cohort study performed at a German tertiary referral centre. At the time of enrolment, patients will be categorised as: (1) newly diagnosed overt CS, (2) recurrent overt CS, (3) CS in remission, (4) presence of mild autonomous cortisol excess (MACE). The target cohorts will be *n* = 40 (groups 1 + 2), *n* = 80 (group 3), and *n* = 20 (group 4). Patients with overt CS at the time of enrolment will be followed for 12 months after remission (with re-evaluations after 6 and 12 months). At each visit, patients will undergo transthoracic echocardiography, cardiac magnetic resonance imaging, 24-h electrocardiogram, 24-h blood pressure measurement, and indirect evaluation of endothelial function. Furthermore, a standardised clinical investigation, an extensive biochemical workup, and a detailed assessment of quality of life and psychosocial status will be applied. Study results (e.g. cardiac morphology and function according to transthoracic echocardiography and cardiac magnetic resonance imaging; e.g. prevalence of CV risk factors) from patients with CS will be compared with matched controls without CS derived from two German population-based studies.

**Discussion:**

CV-CORT-EX is designed to provide a comprehensive overview of the health status of patients with endogenous CS, mainly focussing on CV aspects, and the holistic changes following remission.

**Trail registration:**

ClinicalTrials.gov (https://clinicaltrials.gov/) NCT03880513, registration date: 19 March 2019 (retrospectively registered). Protocol Date: 28 March 2014, Version 2.

## Background

Endogenous Cushing’s syndrome (CS) is a rare disease with an annual incidence of about 4 cases per 1 million inhabitants. In around 80% of cases, the pathognomonic glucocorticoid excess is due to an inappropriate secretion of adrenocorticotropic hormone (ACTH) by a pituitary adenoma, whereas ectopic and adrenal tumours (with concomitant ACTH- or cortisol-over-secretion) are responsible for 10% of cases each [1, 2].

Irrespective of the underlying aetiology, CS patients usually present with a typical clinical phenotype (including facial plethora, proximal myopathy, purple striae, and easy bruising) and suffer from various comorbidities, including relevant cardiovascular (CV) risk factors like arterial hypertension, diabetes mellitus, and dyslipidaemia [3, 4]. The latter are likely to contribute to increased CV morbidity in CS patients, as outlined by prevalences of more than 40% for myocardial hypertrophy [5, 6], up to 30% for arteriosclerosis [7–9], and up to 5% for congestive heart failure [10, 11]. Multiple studies reported an increased mortality risk even after remission of CS. Patients mainly died of CV disease, which is probably explained by their higher incidence of myocardial infarction and ischaemic stroke compared to the general population [1, 12–16].

Physical changes, associated comorbidities, and reduced life expectancy may relevantly compromise personal well-being. Consistently, it has repeatedly been shown that more than half of CS patients suffer from impaired quality of life (QoL) or neuropsychiatric disorders [17–19].

It is thus intuitive to speculate that only an overarching understanding of the underlying pathophysiological mechanisms will enable appropriate and person-centred treatment of endogenous CS. Former studies, however, were often restricted to single clinical aspects (e.g. CV, biochemical, or psychosocial features) or diagnostic tools (e.g. either echocardiography or cardiac magnetic resonance imaging (MRI) for the evaluation of cardiac morphology and function). A more comprehensive diagnostic approach would certainly be favourable.

This study was designed to systematically characterise the effects of endogenous CS primarily on CV morphology and function, but also on physical impairment, biochemistry, and psychosocial status. To serve this goal, an expansive arsenal of diagnostic tools will be applied. The findings should then be put into context with various clinical, biochemical, and psychosocial measures. Of note, in order to assess the potential reversibility of dysfunctionalities after remission of endogenous CS, patients with overt disease will undergo re-evaluation after 6 to 12 months (i.e., with overt CS at baseline and with CS in remission during follow-up). Besides, CS patients will be matched to controls without CS out of the general population. For this, two large population-based control groups derived from the general population in different parts of Germany will be used: Characteristics and Course of Heart Failure Stages A-B and Determinants of Progression (STAAB) [20] on the one hand, and Study of Health in Pomerania (SHIP) [21] on the other.

## Design and methods

### Subjects

#### Patients with endogenous Cushing’s syndrome

Patients with endogenous CS of any aetiology (i.e. pituitary adenoma, ectopic tumour, or adrenal adenoma / hyperplasia) will be considered eligible if the inclusion and exclusion criteria (given in Table 1) are fulfilled. In contrast, patients with iatrogenic CS or adrenal carcinoma will not be enrolled, as the course of the disease is expected to result in a different clinical picture and outcome.

**Table 1 Tab1:** Inclusion and exclusion criteria for the CV-CORT-EX study

**Inclusion criteria:**	
• Patients with the initial, recurrent or former diagnosis of endogenous CS of any aetiology:	
- ACTH-dependent CS (i.e. due to a pituitary adenoma or an ectopic tumour)	
- ACTH-independent CS (i.e. due to an adrenal adenoma or hyperplasia)	
• Patients with MACE, defined as the combination of an adrenal mass and a pathological 1-mg-DST serum cortisol of ≥1.8 μg/dl, but noclinical evidence of overt CS	
• Age ≥ 18 years	
• Written informed consent	
**Exclusion criteria:**	
• Current glucocorticoid pharmacotherapy (except hydrocortisone substitution therapy, usually applied after surgery for CS) or systemic glucocorticoid pharmacotherapy for > 12 months within the previous 3 years	
• Structural heart disease or chronic heart failure (NYHA > II)	
• Organ disease potentially affecting cardiac function	
• ECOG status > 2	
• Former or ongoing malignant diseases (including adrenocortical cancer) treated with (potentially) cardiotoxic therapy	
• Arterial hypertension (uncontrolled despite > 3 antihypertensive drugs)	
• Pregnancy	
• Incompliance suspected or demonstrated	
• Chronic renal failure (MDRD < 60 ml/min)	

*Abbreviations*: *ACTH* adrenocorticotropic hormone, *CS* Cushing’s syndrome, *DST* dexamethasone suppression test, *ECOG* Eastern Co-operative Oncology Group, *MACE* mild autonomous cortisol excess, *MDRD* modification of diet in renal disease, *NYHA* New York Heart Association

At study start, endogenous CS may either be overt or in remission. Care will be taken that former diagnosis of CS was made according to published guidelines [22]. Cases with adrenal disease (i.e., an adenoma or hyperplasia), inadequate response (i.e., a serum cortisol of ≥1.8 μg/dl) during the 1 mg overnight dexamethasone suppression test (1-mg-DST), and no clinical features of CS will be classified as mild autonomous cortisol excess (MACE) [23].

Study-specific investigations will be performed during regular visits at the Division of Endocrinology (University Hospital Würzburg). In case of contraindications for a diagnostic procedure (e.g. metallic implants not allowing for a cardiac MRI), patients will not undergo the particular procedure but will still be able to participate in the study. The same applies for patients who are not able or not willing to undergo certain procedures (e.g. inability to perform a chair rising test due to severe myopathy).

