**Secondary study objectives:**	
• Cardiac morphology and function (using transthoracic echocardiography and cardiac MRI)	
• Endothelial function (using Endo-PAT2000)	
• Blood pressure (using resting and 24-h blood pressure measurement)	
• Heart rate variability profile (using resting and 24-h electrocardiogram)	
• Clinical features (waist-to-hip ratio, body mass index, bio-impedance analysis)	
• Muscle strength (chair rising test, hand grip strength)	
• Biochemistry (including hormonal, metabolic, cardiac and routine parameters)	
• Evaluation of QoL and psychosocial status (using six questionnaires):	
- Disease-specific QoL (CushingQoL, Tuebingen CD-25)	
- Generic QoL (SF-36)	
- Generic health status (EQ-5D-3L)	
- Anxiety (GAD-7)	
- Depressive and panic disorders (brief PHQ-D)	
• Comparison between patients with CS and controls without CS (i.e. from STAAB and SHIP-Trend)	
• Comparison between patients with overt CS and patients with CS in remission	

*Abbreviations*: *CS* Cushing’s syndrome, *LV* left ventricular; *MRI* magnetic resonance imaging, *QoL* quality of life, *SHIP-Trend* Study of Health in Pomerania-Trend, *STAAB* Characteristics and Course of Heart Failure Stages A-B and Determinants of Progression

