#### Evaluation of muscle strength

The possibility of myopathy will be indirectly evaluated by measurement of hand grip strength. Patients will grasp a hydraulic Jamar handgrip dynamometer (Patterson Medical, Warrenville, IL, USA) with the arm right-angled and at maximum force. The arithmetic mean of three readings will be calculated for each hand. Limbs with known muscle dysfunction (e.g. due to a former stroke) will be excluded from the analysis.

In addition, each patient will undergo a chair rising test as described elsewhere [26]. In short, patients are asked to rise from a sitting position at a chair of 45 cm height until full knee and hip extension. The arms must be kept crossed over the chests while performing the chair rising test. Five repetitions at maximum speed should be performed starting in sitting and ending in standing position. The read-out is the time needed to execute the task, with longer durations corresponding to more severe muscle weakness and a higher risk of falls [26].

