#### Data collection and management

Source data are the electronically generated original results of technical examinations, including biochemical analyses. The responsible study team (including physicians and nurses) will enter all collected data into case report forms (CRFs). Missing investigations or data in the CRFs will be flagged, along with a statement on the specific reason. Corrections will be made in accordance with Good Clinical Practice (GCP) guidelines, i.e. the version to be corrected will be crossed out so that it is still legible. The corrections (or other entries) will be marked with the date, hand sign and, if necessary, the reason for the changes conducted by the investigator. Incorrect entries will not be covered with correction fluid, erased, or otherwise rendered illegible. Finally, all data will be transferred into an excel file by the responsible study team. The investigator will maintain a patient identification list which will enable the unique assignment of patient numbers to patient name, date of birth, and sex.

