#### Statistical considerations

Results will be interpreted on the basis of a complete-case analysis. Missing data or investigations that cannot be interpreted will be excluded. Distribution of data will be evaluated by the Shapiro-Wilk test and quantile-quantile plots, as appropriate. Data will be reported by mean (SD), median (quartiles), and count (percent), as appropriate. Χ^2^-test, Mann-Whitney U-test or Kruskal-Wallis test will serve to compare groups. Changes from baseline to follow-up will be assessed using Wilcoxon’s signed-rank test. Univariable associations will be analysed with the Spearman’s rho coefficient. ANCOVA models and multivariable linear regression models will be applied to examine the impact of cofactors or potential confounders on crude or change variables.

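### Chair rising test: patients too weak to rise are dropped as missing, which biases the overt-versus-remission and before/after comparisons of this secondary measure toward no difference

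*Protocol article*

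**What the plan says.** Four places in the protocol article bear on this.

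- **Subjects, text after Table 1.** A patient with a contraindication skips that procedure and stays in the study. Then: "The same applies for patients who are not able or not willing to undergo certain procedures". The example given is "inability to perform a chair rising test due to severe myopathy". Inability and unwillingness fall under one rule.
- **Evaluation of muscle strength.** The test is five rises at maximum speed. "The read-out is the time needed to execute the task, with longer durations corresponding to more severe muscle weakness". No value or category is given for a patient who cannot complete it.
- **Statistical considerations.** "Results will be interpreted on the basis of a complete-case analysis". "Missing data or investigations that cannot be interpreted will be excluded". No exception is made.
- **Data collection and management.** "Missing investigations or data in the CRFs will be flagged, along with a statement on the specific reason". No use of that reason in the analysis is stated.

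Table 2 lists the chair rising test as one of two measures under a secondary objective: "Muscle strength (chair rising test, hand grip strength"). The comparison of overt disease with remission is a secondary objective in the same table.

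**The concern.** A patient who cannot rise because of myopathy lies beyond the slow end of the time scale. That is an observed result, and the most severe one possible. Under the plan it yields no time, counts as missing and is excluded, so the severity of the measured condition decides who stays in the analysis.

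Inability should be commoner in overt disease than in remission. Removing it then makes the overt group look stronger than it is and narrows the contrast. In the longitudinal arm, a patient who cannot rise at baseline but can after remission has no baseline time and leaves the signed-rank test, although this is among the largest recoveries the study could record.

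**Working it through.** **The plan's own figure.** The target cohorts add up: 40 + 80 + 20 = 140. There is no alpha, power or effect size to reproduce, because the study is declared explorative. The point does not touch the 140.

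**Inputs.** From the article: 40 overt and 80 remission patients; Mann-Whitney for groups; Wilcoxon signed-rank for change; complete-case exclusion. Assumed, because the article gives neither: a true difference d of 0.6 SD, and a share u of overt patients unable to do the test. Also assumed: a latent normal weakness score with SD 1, one common threshold above which nobody can do the test, and a two-sided 5% level.

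**Difference among completers.** Let z be the (1 − u) normal quantile and t = d + z the threshold. Then

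- overt completers' mean = d − φ(z)/(1 − u)
- remission completers' mean = −φ(t)/Φ(t)

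With d = 0.6:

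| Overt unable | z | t | Overt mean | Remission mean | Difference |
|---|---|---|---|---|---|
| 2.5% (1 of 40) | 1.960 | 2.560 | 0.6 − 0.0584/0.975 = 0.540 | −0.0151/0.9948 = −0.015 | 0.56 |
| 5% (2 of 40) | 1.645 | 2.245 | 0.6 − 0.1031/0.95 = 0.491 | −0.0321/0.9876 = −0.033 | 0.52 |
| 10% (4 of 40) | 1.282 | 1.882 | 0.6 − 0.1755/0.90 = 0.405 | −0.0679/0.9701 = −0.070 | 0.47 |
| 20% (8 of 40) | 0.842 | 1.442 | 0.6 − 0.2800/0.80 = 0.250 | −0.1411/0.9253 = −0.153 | 0.40 |

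Simulation gives the same values to within about 0.01 SD (0.53 at 5%).

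**Mann-Whitney power** (simulated, 2,000 to 3,000 runs per setting, so good to a point or two):

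| Overt unable | Unable dropped | Unable ranked worst |
|---|---|---|
| 2.5% | about 81% | about 85% |
| 5% | about 80% | about 85 to 86% |
| 10% | about 74% | about 85% |
| 20% | about 60% | about 84% |

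**Other effect sizes.** For true differences of 0.4 to 0.6 SD and 5 to 20% unable, the difference shrinks by about 12% (0.60 to 0.53) to 36% (0.50 to 0.32). Power falls by about 6 points (85 to 79%) to 24 points (85 to 61%).

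**Looser link between inability and score.** If inability correlates 0.7 with the score instead of cutting it exactly, d = 0.6 gives:

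- 10% unable: 0.53 SD; power 78% against 84%.
- 20% unable: 0.50 SD; power 70% against 81%.

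**Paired change.** Assumed true change 0.5 SD, correlation 0.6 and 40 pairs (the most the overt target allows). At 5, 10 and 20% unable at baseline:

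- The completers' change is 0.47, 0.45 and 0.42 SD.
- Signed-rank power is 88, 84 and 74%, against 92, 91 and 89% when the unable are given the threshold value as a worst score.

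**The case against.** **A reader might infer that severe myopathy vanishes from the muscle-strength results altogether.** The article does not support that. Hand grip strength is measured separately, and a patient who skips one procedure stays in the study. Only the chair rising time is lost.

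**A reader might take the 40 to 80% in the Discussion as the share affected.** That figure is the prevalence of proximal myopathy in overt disease, not of inability to complete five rises. Table 1 also excludes ECOG status above 2, which may remove some of the most disabled patients. Rates well below 10% are plausible, and at 2.5 to 5% the power loss is only about 4 to 6 points. The strict threshold is also the unfavourable case.

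**Scoring rules are often left to an analysis plan.** This carries some weight: the reason is recorded, and counts with a chi-square test are among the planned methods, so the proportion unable could be tabulated. But the article does not leave the matter open. It fixes complete-case exclusion without exception and itself names the case to which that rule applies badly. An analysis plan that follows it inherits the problem.

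**A worst rank is not free.** This stands. It does not carry over directly to the signed-rank test, which ranks within-patient differences, or to linear models on times. It also requires deciding whether weakness, rather than pain, joint disease or refusal, was the cause.

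**The measure is minor.** This stands too: it is one of two measures under one of many secondary objectives in an explorative study.

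**Conclusion.** The point holds for the chair rising test. As written, the plan excludes patients who cannot rise because of severe myopathy, and this biases the overt-versus-remission and before/after differences toward zero. The direction rests on inability being commoner in overt disease, which the article's own example and its myopathy figures make likely.

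The size is uncertain because no inability rate is given. At an assumed 0.6 SD it runs from slight (2.5% unable: about 0.56 SD and 4 power points lost) to substantial (20% unable: about 0.40 SD and 24 points lost), and is smaller if inability follows the score loosely. The paired loss is modest at 5 to 10% unable. This is a worthwhile, cheap improvement to one secondary measure; no primary conclusion depends on it.

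**What to change.** Add to Statistical considerations that not performing or not completing the chair rising test because of muscle weakness, as given by the reason in the CRF, is an outcome and not missing data. Then:

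1. Report the proportion unable by group and visit.
2. In the Mann-Whitney and Kruskal-Wallis tests, give these patients a tied worst rank.
3. In the signed-rank test, give them one common value beyond the slowest observed time. Set it far enough out, by a rule fixed in advance, that a change from unable to able counts among the largest improvements and the reverse among the largest deteriorations. Unable at both visits counts as no change.
4. Treat refusal and unrelated causes as missing.
5. State that ANCOVA and linear regression on times describe completers only, or use a rank-transformed outcome.

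**Cost.** A few sentences and no new measurement, since the reason is already recorded. The downsides are that the article sets no standard categories for that reason, so it must be classified consistently, and that the result is no longer a pure time measure.

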#### Control subjects

In order to elucidate the effects of endogenous CS, results from affected patients and controls without CS will be compared (e.g. evaluating their respective cardiac morphology and function, as described by transthoracic echocardiography and cardiac MRI). For this, subjects from two German population-based studies will be matched for possible contributors (mainly age, gender, and hypertension). A matching ratio of 1:2 (patients with CS to controls without CS) will be aimed for.

Prospective Characteristics and Course of Heart Failure Stages A-B and Determinants of Progression (STAAB) cohort study is a population-based study of inhabitants aged 30 to 79 years from the general population of Würzburg (Germany) [20]. STAAB includes a representative cohort of 5000 men and women without previous history of heart failure at baseline. As the echocardiographic workup in STAAB and CV-CORT-EX will be identical (i.e., the same investigators will apply the same diagnostic tools according to standardised operating procedures), even subtle effects of glucocorticoid excess on echocardiographic parameters will hopefully be detected [20, 24].

The Study of Health in Pomerania-Trend (SHIP-Trend) is a population-based, longitudinal study conducted in North-East Germany [21]. It is based on a representative sample including adult men and women aged between 20 and 79 years from the study region. Baseline examinations were conducted in 4420 men and women between 2008 and 2012. This study will particularly be used to elucidate differences in the cardiac MRI of patients with endogenous CS and controls without the disease.

In addition, data from both population-based studies will also be used to compare the results from other diagnostics applied in the CV-CORT-EX study (e.g. from 24-h ECG, 24-h blood pressure monitoring, and questionnaire assessment).

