#### Objectives

CV-CORT-EX aims to comprehensively describe CV health as well as CV related comorbidities in patients with endogenous CS. In particular, our intention is to assess the association of presence and magnitude of glucocorticoid excess to the extent of left ventricular (LV) impairment. Our present data will be compared with those obtained from a control group (matched for relevant contributors like age, sex, and hypertension). Table 2 summarises primary and secondary objectives of the study.

**Table 2 Tab2:** Primary and secondary study objectives

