## Discussion

Endogenous CS is associated with various CV risk factors leading to increased CV morbidity and mortality [2]. So far, studies reporting on CV outcome in patients with endogenous CS primarily focused on particular pathogenic aspects, applied single diagnostic tools, and had a cross-sectional rather than a longitudinal approach. The CV-CORT-EX study aims for a comprehensive CV, biochemical, and psychosocial workup of a representative number of cases with endogenous CS.

Arterial hypertension is quantitatively the most important modifiable risk factor for premature CV disease [35, 36]. It is present in up to 85% of patients with CS, and these numbers are independent of the underlying CS subtype [36]. As endogenous CS is also associated with other relevant risk factors for the development of atherosclerosis (e.g. diabetes mellitus, dyslipidaemia, chronic inflammation, endothelial dysfunction) [4, 35, 37–39], it is no surprise that an increased intima media thickness of the common carotid (as an indicator of atherosclerotic damage) has already been described in such cohorts [7, 9].

Accordingly, non-selected screening for atherosclerosis appears reasonable in case of endogenous CS. Ultrasound (e.g. of the common carotid) is observer-dependent and rather time-consuming. The fact that endothelial dysfunction is known as an early indicator of cardiovascular disease is the rationale for the use of Endo-PAT2000 device in the CV-CORT-EX study. Of note, progression of atherosclerotic plaques over time (with the consequence of slow luminal narrowing) may affect not only peripheral, but also coronary and cerebral arteries [37, 40]. Consequently, if multidetector computerised tomographic coronary angiography was applied to a cohort of CS patients, significantly more (non-) calcified coronary plaques than in a control group were observed [41].

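### Controls are matched on hypertension, which the protocol presents as largely a consequence of Cushing's syndrome, so the control comparison shows only the effect not running through hypertension

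*Protocol article*

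**What the plan says.** Hypertension is named as a matching variable in two places. Control subjects: "subjects from two German population-based studies will be matched for possible contributors (mainly age, gender, and hypertension". Objectives: "matched for relevant contributors like age, sex, and hypertension". The intended ratio is one patient to two controls, drawn from STAAB and SHIP-Trend.

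The purpose is stated broadly: "In order to elucidate the effects of endogenous CS, results from affected patients and controls without CS will be compared". Nothing restricts the target to effects that are independent of blood pressure. No second control set matched on age and sex alone is described.

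The Abstract adds, among its examples of what will be compared, that "prevalence of CV risk factors) from patients with CS will be compared with matched controls without CS". The section on medical history and CV risk factors lists hypertension among those risk factors and defines it as a yes/no status. Control subjects also says that data from both population studies will be used for 24-h blood pressure, without saying whether the matched subset is meant.

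Table 2 places the comparison with controls among the secondary objectives.

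**The concern.** Matching removes differences in the matched variable. That helps when the variable is a common cause of exposure and outcome. It works against the stated aim when the exposure produces the variable and the variable in turn produces the outcome.

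The protocol describes hypertension mainly in the second way. If CS raises LV mass partly by raising blood pressure, controls chosen to have the same hypertension status have that part of the damage built in. The contrast is then smaller than the effect of CS, and nothing in the protocol tells the reader so. A harm acting through blood pressure could be reported as little or no difference from controls. Separately, the plan would compare hypertension prevalence between groups that were selected to be equal on it.

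**Working it through.** **Where the protocol places hypertension**

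- Background: CS patients "suffer from various comorbidities, including relevant cardiovascular (CV) risk factors like arterial hypertension, diabetes mellitus, and dyslipidaemia". On these risk factors it continues: "The latter are likely to contribute to increased CV morbidity in CS patients", with myocardial hypertrophy as the first example.
- Discussion: "Endogenous CS is associated with various CV risk factors leading to increased CV morbidity and mortality". On hypertension: "It is present in up to 85% of patients with CS".
- Discussion, on remission: several studies are cited in which hypertension became less frequent once CS was in remission.

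Together these describe the chain CS → hypertension → cardiac change. Set against the broad aim in Control subjects, matching on hypertension answers a narrower question.

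**Prevalence of hypertension.** If controls are matched exactly on yes/no hypertension, prevalence is the same in both groups and the difference is 0 whatever the truth. Without that matching, taking 85% in CS and an assumed 30–50% in controls:

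- 85 − 50 = 35 points
- 85 − 30 = 55 points

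With 40 overt CS patients against 80 controls (two-sided 0.05, pairing ignored), power to detect such a difference is at least 98%.

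**LV measures.** The protocol gives no effect size, SD or power, so there is no figure to reproduce. The following is an illustration.

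Inputs:
- p1, hypertension in CS: 0.85 (protocol, an upper figure)
- p0, hypertension in age- and sex-matched controls: 0.30–0.50 (assumed)
- h, effect of hypertension on the LV measure: 0.3–0.7 SD (assumed)
- d, effect of CS not through hypertension: 0.2–0.4 SD (assumed)

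Formulas:
- part through hypertension = (p1 − p0) × h
- total difference = d + (p1 − p0) × h
- difference after matching on hypertension = d
- share removed = (p1 − p0) × h ÷ total

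| Case | p0 | h | d | Through hypertension | Total | After matching | Share removed |
|---|---|---|---|---|---|---|---|
| Smallest share | 0.50 | 0.3 | 0.4 | 0.35 × 0.3 = 0.105 | 0.505 | 0.40 | 21% |
| Central | 0.40 | 0.5 | 0.4 | 0.45 × 0.5 = 0.225 | 0.625 | 0.40 | 36% |
| Largest share | 0.30 | 0.7 | 0.2 | 0.55 × 0.7 = 0.385 | 0.585 | 0.20 | 66% |

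A simulation of the central case gave 0.62 SD unmatched and 0.40 SD matched. For 40 against 80 (same simplifications), power in that case falls from about 90% to 54%.

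**Dependence on the patient group.** The removed part is proportional to p1 − p0. If the central gap were half as large, it would be 0.225 × 0.5 = 0.1125 SD, and the share 0.1125 ÷ 0.5125 = 22%. This matters because (80 + 20) ÷ 140 = 71% of the target sample is in remission or has mild autonomous cortisol excess, where the 85% figure may not apply.

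**The case against.** Several points on the other side stand.

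- **A hypertension-matched contrast is legitimate.** It addresses the effect not explained by hypertension, provided no unmeasured factor confounds hypertension and outcome. The protocol shows interest in that question: it hopes to detect subtle glucocorticoid effects on echocardiography, and its Discussion cites work using hypertensive controls and raises a direct cardiotoxic effect. The fault is that this contrast is the only one described and is not labelled.
- **Some hypertension may precede CS or be unrelated to it.** Matching then removes genuine confounding. The documents do not give the share, so calling hypertension purely a mediator would go too far.
- **The prevalence contradiction is narrow.** It rests on an example in the Abstract and affects hypertension only. Diabetes, dyslipidaemia and smoking are not named matching variables.

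A reader might also infer four stronger conclusions that the documents do not support.

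- *The primary analysis is biased.* The four primary objectives describe cardiac measures and name no controls. The follow-up from overt disease to remission, and the comparison of overt CS with CS in remission, do not use controls.
- *The matched difference in LV hypertrophy is zero.* That requires CS to have no effect outside hypertension. The Discussion cites a study that found more fibrosis and poorer systolic and diastolic performance in CS than in hypertensive controls.
- *The 24-h blood pressure comparison is also fixed at zero.* The text does not say that it uses the matched subset. Even if it does, a continuous reading can still differ between groups with the same yes/no status.
- *The choice cannot be undone.* Controls come from cohorts of 5000 and 4420 people, so another set can be drawn.

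**Conclusion.** The concern holds in a limited form. For a secondary objective, the plan matches on a variable that it presents as largely produced by CS, and so estimates a narrower effect than the one it says it wants. Under exact matching, the hypertension prevalence comparison carries no information. Blood-pressure contrasts are pulled towards zero, without reaching it by construction, if the matched set is used for them.

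The loss in LV measures is about 21–66% of the total difference under the assumed ranges. Only the 85%, the 1:2 ratio and the target of 40 overt patients come from the protocol. The 85% is an upper figure, and patients with hypertension uncontrolled on more than three drugs are excluded, so these results lean towards the high end and will be smaller where hypertension is rarer. The direction needs only that CS raises hypertension and hypertension worsens the LV measure, both of which the protocol's own account supports.

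This should be fixed, but it does not undermine the study as a whole.

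**What to change.** 1. Add a control draw from STAAB and SHIP-Trend matched on age and sex only. Use it for the total-effect CS-versus-control contrast and for all comparisons of hypertension, other risk factors and blood pressure.
2. Keep the hypertension-matched contrast, or a hypertension-adjusted model, and label it as the effect not explained by hypertension. Do not compare hypertension prevalence in that set.
3. State in Control subjects and Objectives which control set serves which comparison, including 24-h blood pressure.

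The cost is one more draw from existing cohort data, one more table and some rewording. The drawback is that the age- and sex-matched contrast may carry some hypertension unrelated to CS. That is the reason to report both contrasts rather than replace one with the other.
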